**Protocol**

**Evaluation of efficacy and safety of ethanolamine oleate in sclerotherapy in patients with venous malformations: A multicenter, open-label, single-arm study (EO-1)**

Summary of Protocol

| Title | A Multicenter, open-label, single-arm study to evaluate the efficacy and safety of sclerotherapy with ethanolamine oleate for venous malformations |
| --- | --- |
| Clinical phase | III |
| Objectives | To evaluate the efficacy and safety of sclerotherapy with ethanolamine oleate in patients with difficult-to-resect venous malformations when treated. |
| Trial design | Multicenter, open-label, single-arm |
| No. of patients | 44 cases (22 cystic lesions, 22 diffuse lesions) |
| Target disease | Difficult-to-resect venous malformations |
| Inclusion criteria | 1. No age limitation  2. Signed informed consent from patient or legal guardian(s) (In case age of patient is under 20 years old)  3. Venous malformations are considered difficult to remove, and sclerotherapy is considered first line treatment option by investigator/subinvestigator. Difficulty to remove means a high risk of functional dysfunction due to excision, or a loss of appearance to affect in daily life.  4. Patients who have one or more target venous malformations with a major axis of 30 mm or more in extremities, and 20 mm or more in head and neck region on MRI or CT  5. No thrombus and organized tissue that affects image evaluation or effect judgment in target venous malformations |
| Exclusion criteria | 1. Patients with multiple organ failure or DIC (Disseminated intravascular coagulation)  2. Patients who are taking or have taken drugs that may affect resolution of lesions (propranolol, herbal medicines [such as Kamishoyosan, Ninjinyoeito, Eppikajutsuto or Ogikenchuto], or sirolimus). However, patients can participate in the clinical study in case herbal medicines are discontinued 2 weeks or more before study drug administration.  3. Patients with diabetes mellitus with HbA1c>=8.0, or autoimmune disorder  4. Patients with hepatic dysfunction grade C (10-15 points) in Child-Pugh classification  5. Patients with renal dysfunction with eGFR < 60mL/min/1.73m2  6. Patients with cardiac dysfunction with over grade II in NYHA classification  7. Patients who received sclerotherapy within 6 months prior to obtaining consent  8. Patients with history of allergy to ethanolamine oleate or angiographic X-ray contrast agent as concomitant drugs  9. Patients who have undergone surgery longer than 45 minutes within 2 weeks prior to obtaining consent  10. Patients participating in other clinical study within 4 weeks before obtaining informed consent  11. Pregnant women, women who may be pregnant, or lactating women  12.Patients who are judged as inappropriate by investigator/subinvestigator |
| Test drug | Ethanolamine oleate (investigational new ingredient symbol: FO-611) |
| Dose | Injection of 5% ethanolamine oleate which is double diluted by contrast or normal saline for the venous malformation, within maximum dosage of 0.4 mL/kg. Same method of administration is performed for children (under 15 years of age). Maximum volume of the drug in once treatment is 30 mL after preparation. |
| Mode of administration | Intravenous administration (puncture directly into the lesion) |
| Duration of treatment | Single dose. However, for diffuse lesions, additional treatment may be performed once if necessary. |
| Observational period | Three months per case. However, in cases where additional treatment were given, the period is 3 months after the final administration. |
| Efficacy endpoints | The efficacy evaluations below refer to the case of single administration. If additional treatment is given, evaluation is conducted 3 months after additional administration (1 month after additional administration for number 2 in "2.2 Other secondary endpoints" below) compared to that before the first administration.   1. Primary Endpoint   20% or more reduction in volume of venous malformations at the time of 3 months after intervention   1. Secondary endpoint   2.1 Significant secondary endpoint  Improvement in symptoms such as pain originated from venous malformations at the time of 3 months after intervention  2.2 Other secondary endpoints  1) Reduction rate in volume of venous malformations at the time of 3 months after intervention  2) Improvement in symptoms such as pain originated from venous malformations at the time of 1 months (4 weeks) after intervention  3) Improvement of QOL (ADL) at the time of 3 months after intervention   1. Other endpoints   Change in appearance at the time of 3 months after intervention; significant improvement, moderate improvement, no change and exacerbation. |
| Safety endpoints | Adverse events, side effects, laboratory values |
| Main statistical methods | Due to differences in disease characteristics, cystic and diffuse lesions will be analyzed separately as separate cohorts for all endpoints.   1. Primary endpoint:   For the number of subjects who achieve more than 20% reduction from baseline (prior to administration) in the volume of venous malformations at 3 months of treatment with the study drug, if the null hypothesis is "the proportion of the population achieving mor than 20% reduction from baseline in the volume of venous malformations at 3 months of treatment with the study drug is less than 20%", a binomial distribution Tests based on the binomial distribution is performed. The significance level is set as 2.5% one-sided. The 95% confidence interval between the proportion of subjects achieving more than 20% reduction from baseline in the volume of venous malformations at 3 months of treatment with the study drug and the proportion based on the score test will also be estimated.   1. Secondary endpoints:   2.1 Important secondary endpoints  For the symptom (pain) score associated with the target lesion at 3 months after intervention, the median -1-fold change from baseline (prior to administration) and its 95% confidence interval will be estimated. Also, a Wilcoxon signed-rank test is performed under a null hypothesis of "the median -1-fold change from baseline to 3 months after intervention in the population is less than or equal to 0." The significance level is set at 2.5% one-sided.  2.2 Other secondary endpoints  1) The median percent reduction from baseline (prior to administration) and its 95% confidence interval for the reduction rate (volume) of the target lesion at 3 months after sclerotherapy will be estimated. Also, a Wilcoxon signed-rank test is performed under a null hypothesis of "The median reduction rate (volume) of the target lesion at 3 months after sclerotherapy is less than or equal to zero. The significance level is set at 2.5% one-sided.  2) The median -1-fold change from baseline (prior to administration) to 1 month post sclerotherapy and its 95% confidence interval for the symptom (pain) score associated with the target lesion at 1 month (4 weeks) post sclerotherapy will be estimated. Also, a Wilcoxon signed-rank test is performed under a null hypothesis of "the median -1-fold change from baseline to one month after sclerotherapy in the population is less than or equal to zero." The significance level is set at 2.5% one-sided.  3) The median change from baseline (prior to administration) to 3 months after sclerotherapy and its 95% confidence interval for the QOL score will be estimated. A Wilcoxon signed-rank test is performed under a null hypothesis of "the median change from baseline to 3 months after sclerotherapy for the population is less than or equal to zero." The significance level is set at 2.5% one-sided.  3. Other evaluation items  The percentage of each category (significant improvement, moderate improvement, unchanged, and exacerbation) for the change in appearance at 3 months after sclerotherapy will be estimated. We will also estimate the percentage of significant improvement or moderate improvement and its 95% confidence interval, under a null hypothesis of "the percentage of cases with significant improvement or moderate improvement is less than 20%." and then perform a test based on the binomial distribution. The significance level is set at 2.5% one-sided.  Main statistical methods  4. safety endpoints:  1) For each adverse event and adverse drug reaction, the number of subjects and incidence rate are shown. The number of subjects and the incidence rate is tabulated by organ, symptoms findings, and grade of adverse event. For serious adverse events, the number of subjects and incidence rate should be indicated and listed.  2) Summary statistics of laboratory measurements are tabulated by survey period. |

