4.1.2　Feature

The characteristics of the investigational drug are as follows

Ingredient symbol: FO-611

Nonproprietary name: Monoethanolamine oleate

Dosage form: liquid/injection

Content: 1.000 g monoethanolamine oleate (0.822 g oleic acid, 0.178 g monoethanolamine) in 1 vial (10 g)

Description: Clear, viscous, colorless to pale yellow injectable liquid

Route of administration: intravenous (direct puncture into lesion)

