4.1.4　Preparation methods and considerations

The following procedure is used to prepare the investigational drug.

1. Remove the flip-off cap of the vial of the investigational drug and clean the surface of the rubber stopper with alcohol cotton.
2. Take 10 mL of water for injection or angiographic X-ray contrast medium as a diluent in a syringe, and inject it into the vial by inserting a needle vertically into the center of the rubber stopper (20 mL volume after preparation).
3. After injection, shake the investigational drug horizontally to confirm that it is uniformly dissolved before use.

Suitability as a diluent is as follows

| Type of diluent | | Suitability as a diluent |
| --- | --- | --- |
| water for injection | | Suitable |
| physiological saline solution | | Unsuitable*. |
| X-ray contrast media for angiography | Iopamidol formulation (iodine content: 300, 370 mg/mL) | Suitable |
|  | Iohexol formulation (iodine content: 300, 350 mg/mL) | Suitable |
|  | I Oxaglic Acid Preparation | Unsuitable*. |
|  | Ioversol formulation (iodine content: 320, 350 mg/mL) | Unsuitable** |
|  | Iomeprol formulation (iodine content: 300, 350, 400 mg/mL) | Suitable |
|  | Iopromide preparation (iodine content: 300, 370 mg/mL) | Unsuitable** |

*: Do not use because it may become cloudy or not reduce viscosity.

**: Do not use as it may become cloudy.

The solution is a clear, viscous, colorless to pale yellow injectable solution.

The shaking during preparation causes minute air bubbles to be dispersed in the solution. After 1-3 minutes of standing, the air bubbles will collect on the surface of the solution. Aspirate the solution into a syringe, taking care to avoid air bubbles on the surface.

This product should be used immediately after mixing with water for injection or angiographic X-ray contrast medium. To avoid bacterial contamination, preparation should be done immediately before use, and residual liquid after use should not be reused.

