4.1.5　Concentration of solution after preparation

Each vial (10 g: 10% ethanolamine oleate) is dissolved in 10 mL of water for injection or angiographic X-ray contrast medium, to make a solution concentration of5% ethanolamine oleate. The total volume after preparation will be 20 mL.

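### The protocol synopsis allows normal saline as diluent, while section 4.1.4 rates physiological saline unsuitable and says not to use it

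*Protocol*

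**What the plan says.** The Dose row of the Summary of Protocol describes the treatment as "Injection of 5% ethanolamine oleate which is double diluted by contrast or normal saline for the venous malformation", with a ceiling of 0.4 mL/kg. It adds: "Maximum volume of the drug in once treatment is 30 mL after preparation".

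Section 4.1.4 gives the preparation in numbered steps. The diluent step reads "Take 10 mL of water for injection or angiographic X-ray contrast medium as a diluent in a syringe". A table of diluents follows. Its saline row reads "physiological saline solution | | Unsuitable", and the footnote to that rating is "Do not use because it may become cloudy or not reduce viscosity". The same table rates water for injection suitable. Of six contrast preparations it rates three suitable (iopamidol, iohexol, iomeprol) and three unsuitable (the oxaglic acid preparation, ioversol, iopromide).

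Section 4.1.5 repeats the diluents and gives the starting strength: "Each vial (10 g: 10% ethanolamine oleate) is dissolved in 10 mL of water for injection or angiographic X-ray contrast medium". It puts the strength after preparation at 5%, in 20 mL.

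**The concern.** The synopsis and the preparation section give different answers to a practical question: what may be mixed with the vial before it is injected into a lesion. One names saline as an option; the other says not to use it. One is silent on water for injection; the other offers it. One says contrast without qualification; the other excludes half of the contrast preparations it lists.

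The synopsis is part of the protocol, and nothing in the text at hand says that the body prevails over it. The trial is multicenter, and the Dose row applies the same method to children. A site that relied on that row could inject a preparation that the protocol's own footnote warns may turn cloudy or stay viscous. That is a safety matter first. For the analysis, it would also mean that the product under test was not prepared in the same way at every site.

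**Working it through.** **Diluent.** No arithmetic applies here; the texts are set side by side.

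| Diluent | Synopsis, Dose row | Section 4.1.4 | Section 4.1.5 |
| --- | --- | --- | --- |
| Normal (physiological) saline | Allowed | Unsuitable, do not use | Not offered |
| Water for injection | Not mentioned | Suitable | Named |
| Contrast: iopamidol, iohexol, iomeprol | Allowed (no limit stated) | Suitable | Contrast named, products not listed |
| Contrast: oxaglic acid preparation, ioversol, iopromide | Allowed (no limit stated) | Unsuitable, do not use | Contrast named, products not listed |

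- The saline row is a direct contradiction: both statements cannot be followed.
- On water for injection and the second contrast row, the synopsis is incomplete rather than opposite. It omits one option that 4.1.4 accepts and does not exclude three that 4.1.4 rejects.
- Only the first contrast row satisfies both texts.

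**Strength.** The inputs are the vial content in section 4.1.2 (1.000 g in 10 g), the 10 mL of diluent in 4.1.4, and the 20 mL total and 5% in 4.1.5. The stated total implies that the 10 g vial is taken as about 10 mL.

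1. Vial: 1.000 g / 10 g = 10%, as 4.1.5 states.
2. After preparation: 1.000 g / (10 mL + 10 mL) = 0.050 g/mL = 5%. The protocol's figure is reproduced.
3. Dilution factor: 10% / 5% = 2. The preparation in 4.1.4 and 4.1.5 is itself a twofold dilution.
4. If the synopsis means a twofold dilution that ends at 5%, it agrees with 4.1.5. If it means a 5% solution that is then diluted twofold, the result is 5% / 2 = 2.5%, a strength stated nowhere in the protocol.
5. The 0.4 mL/kg limit also stands in section 3.1, in 4.1.6, in note 6 to the table in 6.1.1, in note 8 to the table in 6.1.2, and in 6.2.3.1. All five tie it to 5%. Section 4.1.6 also applies the 30 mL ceiling to the prepared solution, in line with the synopsis's own wording on that ceiling.

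**Do the two issues interact?** Not on the stated volumes. Replacing 10 mL of water or contrast with 10 mL of saline leaves 1.000 g in 20 mL, nominally 5%. The diluent conflict concerns the physical quality of the preparation, not the nominal amount of drug.

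**The case against.** The best defence is that the synopsis is only a summary. Section 4.1.4 is the operative instruction: it is detailed, has explicit do-not-use notes and is consistent with 4.1.5, so whoever prepares the vial would be expected to work from it. Contrast is named in both places, and the rationale for exclusion criterion 8 in 3.2.2.3 even describes preparation with contrast as necessary. Contrast therefore looks like the expected diluent, and a suitable contrast medium raises no conflict. All of this stands, and it limits how often the error would reach a patient. It does not remove the contradiction, because the Dose row is current protocol text and names saline as an option.

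Two stronger readings are tempting, and the documents support neither.

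- A reader might infer that the dose limit is attached to two strengths: 0.4 mL/kg x 50 mg/mL = 20 mg/kg at 5%, against 0.4 mL/kg x 25 mg/mL = 10 mg/kg at 2.5%. The arithmetic is right, but it measures a reading that the rest of the protocol speaks against. The only product described is a 10% vial, its twofold dilution gives 5%, and no section describes a 5% stock to be diluted again.
- A reader might infer that every injection prepared from the synopsis breaches 4.1.4. It does not: an injection made with a contrast medium rated suitable in 4.1.4 satisfies both texts.

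**Conclusion.** Wrong as written, on the diluent. The synopsis allows one diluent that section 4.1.4 says not to use, omits one that it rates suitable, and fails to exclude three of the six contrast preparations on its list. The number of injections that could be affected cannot be stated, because the documents do not say how often each diluent would be chosen. The finding needs no such figure, since it rests on the text alone.

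On strength, the synopsis is unclear about whether 5% is before or after the twofold dilution. This calls for clarification; a twofold dose conflict is not shown.

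This review takes no position on which diluent list is clinically right. It says only that the passages disagree and must be reconciled.

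**What to change.** - Reconcile the Dose row with sections 4.1.4 and 4.1.5 so that the protocol carries one diluent list, including which contrast preparations may be used. A cross-reference from the synopsis to the table in 4.1.4, once that table is confirmed, would prevent the two drifting apart again.
- Read the exclusion criterion 8 rationale in 3.2.2.3 in the same pass. It describes contrast as necessary, while 4.1.4 and 4.1.5 also offer water for injection.
- In the same edit, state in the Dose row whether 5% is the strength before or after dilution.
- Notify all sites of the correction.

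Optionally, record the diluent for each treatment. Section 6.2.3.1 asks for the volume given, which cannot show what the drug was mixed with, so a departure could be hard to identify when the per protocol set is decided. Administration records are already source documents (9.4.1) and deviations must already be recorded (9.7), so this is a convenience rather than part of the correction.

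The cost is a synopsis amendment, with the review that any amendment needs, and a site notice. Sample size, endpoints and analysis do not change.

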[11. Funds and conflicts of interest 51](#_Toc117669661)

[11.1 Funds (money) 51](#_Toc117669662)

[11.2 Conflict of interest 52](#_Toc117669663)

[12. Payment of money, etc. and insurance 52](#_Toc117669664)

[12.1 Payment of money, etc. 52](#_Toc117669665)

[12.2 Health damage compensation 52](#_Toc117669666)

[13. Publication arrangements 52](#_Toc117669667)

[14. Organization 53](#_Toc117669668)

[15. References. 54](#_Toc117669669)

Abbreviations (general)

| Abbreviation | Full spell |
| --- | --- |
| ADL | Activities of Daily Living |
| AMED | Japan Agency for Medical Research and Development |
| ARO | Academic Research Organization |
| CR | Complete Response |
| CRO | Contract Research Organization |
| CRF | Case Report Form |
| CSR | Clinical Study Report |
| CT | Computed Tomography |
| DIC | Disseminated Intravascular Coagulation |
| DSA | Digital Subtraction Angiography |
| eGFR | Estimated Glomerular Filtration Rate |
| EQ-5D | EuroQOL 5 dimensions |
| FAS | Full Analysis Set |
| GCP | Good Clinical Practice |
| IRB | Institutional Review Board |
| MRI | Magnetic Resonance Imaging |
| NYHA | New York Heart Association |
| PCA | Passive Cutaneous Anaphylaxis |
| PedsQL | Pediatric Quality of Life Inventory |
| pH | Potential of Hydrogen |
| PPS | Per Protocol Set |
| PR | Partial Response |
| QOL | Quality of Life |
| SAE | Serious Adverse Event |
| SAS | Safety Analysis Set |
| SpO_2_ | Saturaion of Percutaneous Oxygen |
| VAS | Visual Analogue Scale |

Abbreviations (Laboratories)

| Abbreviation | Full spell |
| --- | --- |
| Alb | Albumin |
| ALP | Alkaline Phosphatase |
| ALT | Alanine Aminotransferase |
| AMY | Amylase |
| APTT | Activated Partial Thromboplastin Time |
| AST | Aspartate Aminotransferase |
| BUN | Blood Urea Nitrogen |
| Ca | Calcium |
| CK | Creatine Kinase |
| Cl | Chlorine |
| Cre | Creatinine |
| CRP | C-Reactive Protein |
| FDP | Fibrinogen/Fibrin Degradation Products |
| Glu | Glucose |
| γ-GTP | gamma -Glutamyl Transpeptidase |
| HbA1c | Hemoglobin A1c |
| HDL-chol | High density lipoprotein- Cholesterol |
| IP | Inorganic Phosphorus |
| K | Potassium |
| LDH | Lactate Dehydrogenase |
| Na | Sodium |
| PT | Prothrombin Time |
| PT-INR | International Normalized Ratio of Prothrombin Time |
| T. Bil | Total Bilirubin |
| T-chol | Total Cholesterol |
| TG | Triglyceride |
| TP | Total Protein |
| UA | Uric Acid |

1. Introduction

1.1　Medical background

1) About Venous Malformations

Venous malformation is an abnormality in the formation of vascular vessels during the embryonic period and is associated with symptoms such as pain and movement disorders. The estimated number of patients in Japan (Ministry of Health, Labour and Welfare's Research and Study on Intractable Hemangioma, Hemangiopericytoma, Lymphangioma, Lymphangiomatosis and Related Diseases, Ministry of Health, Labour and Welfare's Research and Policy Project on Intractable Diseases in Fiscal 2014) is approximately 20,000. Half of the estimated 20,000 possess lesions which are considered to be difficult to resect, such as extensive cases or cases with muscle involvement^1)^, and sclerotherapy is the treatment of choice for these patients (number of applicable patients: approximately 10,000).

2) History of the development of this product for venous malformations

In Japan, ethanolamine oleate, anhydrous ethanol, and polidocanol are used in off-label sclerotherapy. Regarding safety, ethanolamine oleate is considered a safe sclerosing agent with few side effects and no serious side effects as shown in a systematic review by Horbach et al (venous malformation or lymphatic malformations) compared to anhydrous ethanol, and polidocanol in which life-threatening side effects have been reported (Jo JY, et al: Cardiovascular collapse due to right heart failure following ethanol sclerotherapy, Frost et al: A case of a child with two cardiac arrests during polidocanol vascular sclerotherapy)^2, 3)^. In 5 studies 188 patients with venous malformations or lymphatic malformations, skin ulceration and skin necrosis [6 cases, 3%] were observed as side effects, but no systemic side effects, facial neuropathy, or other side effects were reported)^4)^. In a study that evaluated the cytotoxicity of each sclerosing agent on muscle tissue, ethanol was the most cytotoxic, with ethanolamine oleate and polidocanol being comparable.^5)^ Efficacy was also reported with ethanolamine oleate showing reduction of lesions and improvement of symptoms in 88-100% of cases^4)^. 83 other cases (85 operations) in which ethanolamine oleate was administered mainly to children (average age 15.1 years: 3 months to 21 years of age) reported complete remission of symptoms in 79 lesions and significant improvement in 6 lesions.^6)^

Sclerotherapy is also a common treatment for venous malformations internationally, and the American textbook on vascular malformations, Vascular Anomalies, describes sclerotherapy as one of the best treatments for venous malformations.^7)^ It also describes various sclerosing agents (including ethanolamine oleate).^7)^ The effectiveness of sclerotherapy for venous malformations is also described in international guidelines such as “Guidelines and parameters: Percutaneous sclerotherapy for the treatment of head and neck venous and lymphatic malformations (VM and LM)” in the United States, and “European guidelines for sclerotherapy in chronic venous disorders” in Europe, particularly in Germany. Although there are a variety of sclerosing agents being used, no sclerosing agent has been approved by the pharmaceutical industry for venous malformations.

Therefore, ethanolamine oleate is considered the best agent as a curing agent in terms of efficacy and safety.

2. Rationale, purpose, and risk/benefit assessment of the clinical trial

